### Eligibility criteria {10}

Patients will be recruited on the ICU of the University Hospital Bonn. The patient inclusion criteria are as follows: (1) The study includes all patients under intensive care monitoring and therapy with a length of stay > 48 h in the surgical intensive care units of the University Hospital Bonn. (2) All participating patients have signed the patient consent form for study participation as well as the privacy policy after comprehensive explanation, explanation and information or have been represented by the spouse as part of the spouse’s emergency representation after comprehensive explanation. (3) Patients aged > 18 years are included. Exclusion criteria for the study are: (1) acute or chronic infections of the extremities, (2) open wounds on the lower extremity, (3) Pregnancy and breastfeeding, (4) sickle cell anemia, and (5) former surgical interventions on the thigh vessels (e.g., stenting, bypassing).

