### Intervention description {11a}

#### Experimental intervention group 1: blood flow restriction/ischemic preconditioning (BFR/IPC) training

The first intervention group receives a daily BFR/IPC intervention of the lower extremities with 100% of the individual limb occlusion pressure (LOP). BFR training involves the application of tourniquets during a passive or active exercise intervention in order to provide an additive metabolic stimulus. The tourniquets are applied as proximal as possible to the thigh and a pressure is applied that temporarily occlude venous return with associated reductions/ complete blocking of arterial inflow [27]. For BFR/IPC training, a CE-certified surgical-grade tourniquet autoregulation device (CE-9–2200-001BFR-C, Delfi Medical Innovations Inc., Vancouver, Canada) is used. The applied exercise pressure is calculated by the individual limb occlusion pressure (LOP) using the BFR/IPC device at the start of each training session. The patient lies in bed at rest while the cuff is inflated until no more blood flow can be detected in the limb (= LOP). From this occlusion pressure, 100% is subsequently applied for the BFR/IPC intervention. The intervention protocol consists of daily exercise sessions of 50 min at intervals, whereby both thighs are exercised alternately (5 min occlusion + 5 min free flow, 5 times in total) over a period of 7 days [28].

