**Fig. 2 Fig2:**
[figure not shown]
Study flow chart

Basal examinations

All participating patients will go through a series of measurements before and after the intervention period of seven continuous days, as well as after discharge of the ICU and discharge of the hospital.Muscle Analysis I (Non-invasive):Muscle mass of the thigh muscles, which represents a correlation to the full body muscle mass [29], and fiber angle will be obtained by ultrasound and analyzed through a software-based post-processing pipeline. To determine grip strength, which shows a positive correlation with total body strength [30], a measurement of both hands is carried out using a hand dynamometer (Dynamo, Vald, Brisbane, Australia). An isometric maximum strength test is performed on both lower extremities during the following exercises: Dorsiflexion of the foot, plantar flexion of the foot, hip flexion, and knee extension. During this process, surface electromyography (Picoblue, Cometa, Bareggio, Italy) is used to analyze neuromuscular activation of the M. rectus femoris and M. vastus lateralis during the exercise.Global Health:For analyzing the global health status of the participating patients, routine laboratory measurements, containing, e.g., inflammation parameters (e.g., C-reactive protein, leucocytes), electrolyte concentrations, parameters of kidney- and liver function, will be measured daily. Additionally, the application of drugs for supporting the cardiovascular system (e.g., noradrenaline), analgesics (e.g., fentanyl), sedation (e.g., propofol), and antibiotics is monitored throughout the 7-day intervention phase as well as directly before and after each intervention training.Hospital length of stay, status at hospital discharge, economic effects:To assess the economic outcomes, data from the §21 Krankenhausentgeltgesetz data will be analyzed to measure and compare length of stay, status at hospital discharge and treatment costs between study groupsHealth-related Quality of Life:Patients are given questionnaires to record their health-related quality of life (Quality of Life, SF36; WHODAS 2.0) [31]. In addition, patients are asked to indicate their current pain perception on a 100-mm VAS.

(2)Continuous examinations

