Muscle Analysis II (Intramuscular, continuous measurements)By implementation of a microdialysis catheter into the M. vastus lateralis before the first basal examination is applied, it is possible to measure metabolic impact (e.g., lactate, glucose, pyruvate) and inflammatory cytokines (e.g., IL-6, IL-8, IL-10, and TNF-α) of the disease, ICU therapy, and study intervention on the muscle tissue continuously. This minimal-invasive technique enables the quantification of the acute influence of the therapy on the muscle tissue and to correlate it with changes in the other dimensions of the endpoints. The catheters are placed under sterile conditions and controlled by ultrasound after local anesthesia. In total, the catheter will stay in the muscle for 8 days. After implementation of the catheter, the flow rate at which the catheter is being flushed with the perfusion solution (NaCl) is set by a pump. During the day, the flow rate will be timed to 1 µl/min to obtain a sample of 180 µl every 3 h. Subsequent analyzation will be performed by ISCUSflex Microdialysis Analyzer (µDialysis, Stockholm, Sweden) and our cooperation partners at the Universitätsklinikum Knappschaftskrankenhaus Bochum, Ruhr-University Bochum.Systemic Immune ResponseIn addition to intramuscular measurements to analyze immune function and responses in the skeletal muscle tissue, we will evaluate the systemic immune response of the intervention. EDTA blood samples will be obtained daily during the intervention period. EDTA blood is drawn and PBMCs are isolated using Ficoll gradient centrifugation. PBMCs are then spun unto a microscope slide (Cytospin) and fixed using formaldehyde solution. Mitochondrial protein interaction for TFAM and TFB2M will be analyzed using proximity ligation assay, as previously described [6]. Briefly, cells are permeabilized and blocked using Intercept TBS Blocking buffer (Licor) and incubated with both primary antibodies overnight. After washing cells are incubated with proximity probes against mouse and goat IgG. Oligonucleotides forming the DNA circle are hybridized and ligated and subsequently amplified using a compaction oligonucleotide (PMID 26202090). PLA signals are detected with fluorescent oligonucleotides and then visualized with a fluorescent microscope.In addition, ATP content of PBMCs is analyzed using the CellTiterGlo Kit (Promega). ROS induction is measured in plasma samples, which is isolated from EDTA blood. ROS is measured using CM-H2DCFDA a fluorescent probe that changes fluorescent spectrum upon oxidation by ROS. In addition, we will measure the cytokine response in serum samples of the patient. Specifically, we will measure the cytokines IL-6, IL-8, IL-10, and TNF-α which are known for their potential role in muscle injury.

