### Recruitment {15}

The University Hospital Bonn has one of the largest surgical intensive care capacities in Germany (88 surgical intensive care beds). In the course of the feasibility study, all patients who meet the inclusion criteria can be enrolled in this study. To extend the inclusion to patients under sedation or mechanical ventilation, the consent to participate in the study by the “Ehegattennotvertretungsrecht” was also added and ethically confirmed. This allows the patient’s legal spouse, if they are not currently able to give consent, to be contacted and informed, and to confirm or decline participation in the study. During the pre-testing phase, a participation rate of 85% was achieved.

The feasibility of recruitment is derived from our experiences with the recruitment in previous intensive care projects. Approximately 3500 cases are treated at our institution’s surgical ICUs annually. Of these, approximately 5–10% have an extended stay < 7 days, making them good candidates for the proposed study. At the current rate of extended stay ICU patients, we expect to screen 25 patients per month. Of these we plan to recruit approximately 5–6 patients per month into the project, which means that in 36 months we can recruit up to 180 patients.

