## Statistical methods

### Statistical methods for primary and secondary outcomes {20a}

#### Data acquisition

All patients will undergo the standardized study protocol. Per each day, measurements will be repeated thrice per time point. The median of these technical replicates will be used as the repeated measurement value for said time point. For descriptive purposes values will be reported as median ± interquartile range or absolute number and percent, where appropriate.

Primary analysis method will be an ANCOVA with Dunnett’s test with the measurement after 7 days as outcome and adjusted for the baseline value. Additionally, mixed models will be fitted to assess the sensitivity of the results under consideration of all measurement points. Health-related quality of life will be analyzed using mixed models for repeated measurements. Again, joint models may be considered to take a considerable proportion of missing data into account. Time-to-event outcomes, such as length of ICU stay, length of hospital stay, and time to return to work, will be analyzed using Kaplan–Meier estimates and Cox regression models.

All primary, secondary, and other exploratory outcomes will also be reported descriptively. Patients who decide to drop out of the study prior to completion of the intervention will remain in the study analysis and their respective study cohort following an intention-to-treat analysis. Recruitment will commence until the overall number of 120.

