### Methods in analysis to handle protocol non-adherence and any statistical methods to handle missing data {20c}

Multiple imputation will be used to take into account missing values, provided data is missing at random. If there is a considerable amount of missing data due to protocol violations or discontinuation, application of joint models will be considered to adequately take this information into account.

Data from patients who withdraw their consent to participate during the intervention period of the study will remain in the analysis. If the patients consent to participate in the follow-ups, they will be analyzed as “intent-to-treat” within their original treatment group allocated by randomization.

Based on our experiences with the SepsisDataNet.NRW cohort (a large multicenter study on sepsis patients), we expect a loss to follow-up (30-day survival) of about 10%. Based on our experience from the health-related quality of life study in ECMO patients (see unpublished data above), we expect a follow-up rate of 75% from patients still alive at the time-point of 6-month follow-up. Due to the expected heterogeneity of the study population, no estimation of mortality in the study group can be done at this point.

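### Entry after a 48 h ICU stay does not secure the day-7 value that the primary analysis needs, and the missing-data rule does not separate death from other missingness

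*Protocol article*

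**What the plan says.** **Entry.** Eligibility criteria {10} include adults "with a length of stay > 48 h in the surgical intensive care units". Nothing is said about how long they are expected to stay from then on.

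**Course and measurement.** Intervention description {11a} plans daily sessions for seven days in each arm. Outcomes {12} adds for the microdialysis catheter: "In total, the catheter will stay in the muscle for 8 days". The basal measurements, which include thigh ultrasound, are taken before and after the seven-day period, "as well as after discharge of the ICU and discharge of the hospital". Statistical methods {20a} makes the primary analysis an ANCOVA with Dunnett's test "with the measurement after 7 days as outcome and adjusted for the baseline value". That section does not name the outcome variable; Sample size {14} sizes the same analysis on muscle thickness.

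**Recruitment.** Section {15} states "Approximately 3500 cases are treated at our institution’s surgical ICUs annually" and then "approximately 5–10% have an extended stay < 7 days, making them good candidates for the proposed study". It derives 25 screened patients per month from this extended-stay group.

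**Missing data.** Section {20c} states: "Multiple imputation will be used to take into account missing values, provided data is missing at random". Joint models are to be considered if much is missing through protocol violations or discontinuation. The same section expects about 10% loss, labelled as 30-day survival, and declines to estimate mortality. Section {20a} keeps patients who drop out before completing the intervention in their randomised group, by intention to treat.

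**Power.** Sample size {14} claims at least 75% per arm with 30 patients per arm, for a follow-up SD of 2 mm and a correlation above 0.9.

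**The concern.** Three parts of the protocol seem to describe different patients. Eligibility takes anyone past 48 h. The course and the primary analysis need patients who can be treated and measured through day 7. The recruitment figures rest on a long-stay subgroup whose printed definition runs against its own name.

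The practical consequence is a missing or undefined day-7 value. A patient can qualify at 48 h and then leave the ICU or die within the week. No section shown says whether sessions continue after an early move to the ward, or whether the final measurement is still taken on day 7. The discharge measurements are tied to discharge dates, not to day 7.

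Death is the harder case. A living patient who was not scanned had a muscle thickness on day 7 that nobody recorded, and imputing it is meaningful. For a patient who died there is no such quantity. The {20c} rule does not make this distinction, and death is also absent from the drop-out reasons listed in {11b}. If the general rule were applied to deaths, the primary contrast would mix measured values with values that have no counterpart. It could be distorted if mortality differs between arms. The power statement also leaves no room for any missing day-7 value.

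**Working it through.** **1. Which pool the recruitment figure describes** (inputs from {15})

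- Extended-stay cases per year: 0.05 × 3500 = 175 to 0.10 × 3500 = 350.
- Per month: 175 / 12 = 14.6 to 350 / 12 = 29.2.
- Stated screening of 25 per month: 25 × 12 / 3500 = 8.6% of cases, inside the 5–10% band.
- Stated recruitment: 5 × 36 = 180 and 6 × 36 = 216, so the printed maximum of 180 matches the lower rate. The 120 patients needed take 120 / 6 = 20 to 120 / 5 = 24 months.

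The screening figure therefore comes from the extended-stay share and not from all stays beyond 48 h. The arithmetic is sound, but it describes a group other than the one in {10}.

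**2. Reproducing the stated power** (inputs from {14})

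- Difference: 2.8 − 2.1 = 0.7 mm.
- Residual SD after baseline adjustment: 2 × √(1 − 0.9²) = 0.872 mm.
- Assumed, because not stated: two-sided familywise alpha of 0.05.
- Dunnett critical value for three comparisons, 4 × 30 − 5 = 115 df: 2.38.
- Noncentrality: 0.7 / (0.872 × √(2/30)) = 3.11.
- Power from the noncentral t distribution: 76.6%. A direct ANCOVA simulation (4,000 runs) gives about 76%.

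This agrees with the plan's figure of at least 75%. It assumes that all 30 patients per arm have a day-7 value.

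**3. The same calculation with fewer day-7 values**

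| Share without a day-7 value | Evaluable per arm | Power | Enrolled per arm to keep 30 evaluable, 30 / (1 − share) |
|---|---|---|---|
| 0% | 30 | 76.6% | 30 |
| 10% | 27 | 71.4% | 34 |
| 20% | 24 | 65.3% | 38 |
| 30% | 21 | 58.4% | 43 |

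Simulation gives about 71%, 64% and 57% for the last three rows. Only the 10% has a source in the protocol, and there it refers to 30-day survival. The 20% and 30% rows are assumptions that show the range. The calculation uses patients with an observed value only.

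**4. The missing-data rule against the possible reasons**

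| Situation at day 7 | What the protocol shown provides |
|---|---|
| Left the ICU, still in the hospital | Measurement possible ({9}, {12}), but not explicitly set for day 7 |
| Left the hospital | Follow-up by telephone ({18b}), so no scan is described |
| Withdrew or broke the protocol | Imputation if missing at random; joint models considered |
| Died | Not named in any rule |

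**The case against.** A reader might infer that the plan will impute muscle values for patients who died. The text does not say so. Imputation is conditional on missing at random, joint models are named in {20a} and {20c} as a possible alternative, and death is mentioned in neither rule. The intention-to-treat sentence in {20a} is also written for patients who drop out. What stands is narrower: nothing in the rule excludes deaths, so it could be applied to them.

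A reader might also infer that early ICU discharge loses the day-7 value. It need not. Study setting {9} places all investigations and sessions in the same hospital, Outcomes {12} plans measurements after ICU discharge, and {20a} does not tie day 7 to being on the ICU. The detailed schedule is in a supplementary table and a figure that are not shown.

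Nor is the recruitment forecast shown to be too high. Counting a narrower group than the eligible one does not inflate it, and {15} calls these patients good candidates without making a long stay a criterion. Requiring an expected stay at entry would need a prognosis and would narrow the population. That is a design trade-off, and in a feasibility trial the share completing seven days is itself a result.

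On power, Trial design {8} disclaims definitive efficacy conclusions, and 0.9 is the edge of the stated correlation range; at 0.95, complete-data power is 97.4%. Both points are fair. Still, {14} relies on this power to pick a promising treatment, and its 75% floor belongs to the edge case.

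Finally, much detail on handling deaths could sit in a statistical analysis plan. But {20c} does state a rule, and that rule as worded leaves the distinction open.

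**Conclusion.** The point holds in limited form. Sections {10} and {15} describe different populations, and the printed inequality in {15} does not fit the word extended. The day-7 measurement is not explicitly secured for patients who leave the ICU early. The rule in {20c} does not separate death from other missingness, so it could be used to create day-7 muscle values for patients who have none.

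The size of the problem is uncertain, because the protocol does not give the share of patients who die or go unmeasured before day 7. At SD 2 mm, correlation 0.9 and an assumed two-sided familywise alpha of 0.05, power is about 77% with complete data. At 10% missing it is about 71%, already below the stated 75%. Larger losses are assumptions. Any bias depends on whether death or discharge differs by arm, which cannot be judged from the document. The change is worth making because it is cheap and the trial status is given as in preparation.

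**What to change.** 1. Reconcile {10} with {15}, including the printed under-7-days wording, and say which population the recruitment figures describe. This does not require a new entry criterion.
2. State that the final scan is taken on day 7 in every living patient, on the ICU or on the ward. Patients who have left the hospital by then and cannot be scanned count as alive but unscanned.
3. In {20c}, limit multiple imputation to patients alive at day 7 but not scanned. Report deaths by arm beside the ANCOVA. Note that a comparison among survivors conditions on an event after randomisation and can itself be biased if mortality differs by arm. Add a sensitivity analysis that keeps all randomised patients and ranks death as the worst outcome.
4. In {14}, state that the 75% applies to complete day-7 data, and give the power at the expected loss.

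The cost is some rewording, a few ward scans, one additional analysis and a slightly less favourable power figure.

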## Interventions

### Explanation for the choice of comparators {6b}

#### Sham-Control Group (Sham-BFR)

The control group is receiving the standard intensive care which also includes a daily physiotherapy session. To reduce the intervention bias, a daily"Sham"BFR intervention is also provided. The"Sham-BFR"intervention is performed in an intermittent manner on both thighs, according to the protocol of intervention group 1 (see below), but with the minimum standard pressure of 20 mmHg. This group serves to demonstrate the"clinically standard"progression of our test subject population and the changes are used as a basis for comparison with our intervention groups.

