#### Experimental intervention group 2: electromyostimulation (EStim)

The second intervention group receives a daily Sham-BFR/IPC intervention of 20 mmHg combined with electrical muscle stimulation training (EStim). For EStim, two self-adhesive electrodes (Axion Medical, Axion GMBH, Villengen-Schwennigen, Germany) are applied to the vastus lateralis muscle and two electrodes to the vastus medialis muscle. The stimulation parameters are as follows: frequency 50 Hz, work cycle 10 s stimulation followed by a 10-s pause and pulse width 400 µ. The EStim protocol is only applied during the occlusion phases of the Sham-BFR/IPC protocol. The intervention protocol consists of daily exercise sessions of 50 min at intervals, whereby both thighs are exercised alternately (5 min occlusion + 5 min free flow, 5 times in total) with the “Sham-BFR/IPC” pressure of 20 mmHg and the additional EStim Protocol over a period of 7 days. There is a coupling between the BFR and the EStim device (Mi-Theta 600; Cefar Compex), which only enables EStim during the phases of occlusion. If the limb is reperfused by releasing the air from the cuff, the EStim signal is interrupted and only reactivated when occlusion resumes.

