#### Experimental intervention group 3: BFR/IPC-Training + EStim

The third intervention group combines BFR/IPC training with 100% of the individual limb occlusion pressure with EStim training. Within this intervention group both previously described interventions will be combined. For BFR/IPC training, 100% of the individual LOP is applied, whereas the EStim parameters are as follows: frequency 50 Hz, work cycle 10 s stimulation followed by a 10-s pause and pulse width 400 µ. The intervention protocol consists of daily exercise sessions of 50 min at intervals, whereby both thighs are exercised alternately (5 min occlusion + 5 min free flow, 5 times in total) over a period of 7 days. There is a coupling between the BFR/IPC and the EStim device (Mi-Theta 600; Cefar Compex), which only enables EStim during the phases of occlusion. If the limb is reperfused by releasing the air from the cuff, the EStim signal is interrupted and only reactivated when occlusion resumes.

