### Criteria for discontinuing or modifying allocated interventions {11b}

Drop-out of a patient from the study: One or more of the following circumstances may lead to a patient discontinuing the study (these patients are counted as drop-outs): Withdrawal of consent by the patients or their legal representatives without giving reasons; Occurrence of an exclusion criterion; Violation of the study protocol.

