### Concealment mechanism {16b}

All potential participants will initially be screened for the eligibility criteria via physical examination on the ICU. Subsequently, all individuals who pass the initial screening and are interested in the study will sign a written informed consent and complete the baseline assessment. Following the baseline assessment, participants will be randomly allocated to one of the four study groups.

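### Exclusion criterion 5 covers only past surgery on the thigh vessels, so current thigh-vessel thrombosis is neither a listed exclusion nor a listed ground for stopping, although two of four arms fully occlude both thighs daily

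*Protocol article*

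**What the plan says.** **Eligibility.** Eligibility criteria {10} admit surgical ICU patients who stay longer than 48 hours and are over 18. Five numbered exclusions follow: limb infection, open leg wounds, pregnancy or breastfeeding, sickle cell anemia and, fifth, "former surgical interventions on the thigh vessels (e.g., stenting, bypassing"). Concealment mechanism {16b} describes how the list is used: "All potential participants will initially be screened for the eligibility criteria via physical examination on the ICU".

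**Cuff.** For intervention group 1 (BFR/IPC), Intervention description {11a} says "The tourniquets are applied as proximal as possible to the thigh" and "From this occlusion pressure, 100% is subsequently applied for the BFR/IPC intervention". For group 3 (combined) it says "For BFR/IPC training, 100% of the individual LOP is applied". The other two arms have a token pressure. The control protocol is the same "but with the minimum standard pressure of 20 mmHg", and the EStim arm gets a "daily Sham-BFR/IPC intervention of 20 mmHg".

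**Stopping.** Criteria for discontinuing or modifying allocated interventions {11b}, repeated under Sequence generation {16a}, name three grounds for drop-out: withdrawal of consent, "Occurrence of an exclusion criterion", and violation of the protocol.

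**The concern.** By writing criterion 5, the investigators themselves treat the state of the thigh vessels as a reason not to apply the cuff. The criterion, however, looks only backwards and only at surgery. A thigh vessel repaired long ago keeps a patient out, while a thigh vessel with a clot in it today does not. Because the stopping rule borrows the same list, the gap runs from screening through all 7 days.

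Safety is among the primary endpoints (Abstract, Methods). The target population includes sedated and intubated patients (Objectives {7}), who may be unable to report symptoms in the leg. At stake is whether screening staff have a written rule before the first full inflation or must rely on individual judgement.

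**Working it through.** No stated statistical figure enters this point, so the check sets the provisions side by side, with a count of the patients exposed.

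**1. Does any listed exclusion reach current thrombosis?** Infection, open wounds, pregnancy or breastfeeding, and sickle cell anemia do not. Criterion 5 requires a past surgical intervention, and a thrombosis is not one. None of the five applies.

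**2. Does another section close the gap?**
- Screening ({16b}) is against the listed criteria and adds no vascular check.
- Coagulation values are assessed daily (Objectives {7}, safety endpoints), but as an outcome with no threshold or action attached.
- The drop-out grounds in {11b} and their repeat refer to the exclusion list, so they inherit the gap.
- Adverse event reporting {22} foresees discontinuing the intervention as an action, but only after an adverse event. Under {11a} the limb occlusion pressure is measured at the start of each session by inflating until no flow is detected. The first full occlusion therefore comes before any such reaction. Thrombosis is not among the expected events listed there.
- Sections {21a} and {23} state that there is no monitoring and no formal auditing, so no outside check is planned.

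**3. Who is exposed?** Sample size {14} gives 30 patients per arm.
- Full-pressure arms: 2 × 30 = 60.
- Share of all patients: 60 / 120 = 50%.

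**4. How much occlusion?**
- Session length: 5 × (5 + 5) min = 50 min, which agrees with the stated 50 minutes.
- Over the course: 7 sessions × 5 cycles = 35 five-minute occlusion cycles per patient, plus the pressure measurement at the start of each session. The text does not say clearly whether the five cycles are per thigh or shared between the thighs. The point does not depend on that.

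**5. What happens to such a patient in the analysis once the list is extended?** Section {11b} would count the patient as a drop-out. Statistical methods {20a} retains patients who themselves decide to leave, and {11c} and {20c} retain those who withdraw consent. A patient stopped because of an exclusion criterion is named in none of these. The fix therefore needs a sentence to keep such patients in the analysis.

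**The case against.** The strongest reply is that this is an omission and not an error. Criterion 5 is correct as far as it goes, nothing contradicts it, and no passage says that thrombosis makes cuffing unsafe. The article calls the procedures safe and well established, uses a certified surgical-grade device and refers to standard operating procedures, where device contraindications may be written down. Patients are examined at screening, consent is taken by clinical supervisors, and vital signs are checked every 10 minutes during a session. The ICU team would know of a diagnosed thrombosis and would often decline to cuff that leg. An undiagnosed one would not be caught by new wording without imaging.

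Much of this stands, and it keeps the weight low. It does not remove the point. Eligibility is not deferred to another document: the article gives a complete numbered list, and its stopping rule depends on that list. The mismatch between a past stent and a present clot is visible from the criterion alone.

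A reader might infer three stronger things that the documents do not support:
- *That femoral cannulas in place are also let through.* This depends on how former and surgical are read. Stenting is given as an example, so the criterion may already reach catheter-based procedures. Excluding everyone with a cannula would also have an unknown recruitment cost.
- *That a given number of such patients will be enrolled or harmed.* The documents give no frequency, and any probability would only restate an assumed one.
- *That staff must go on cuffing a thrombosed leg.* Nothing obliges them to, and the adverse event section allows the intervention to be stopped.

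**Conclusion.** The point holds for current known or suspected thrombosis of a thigh vessel. That condition is neither a listed exclusion nor a listed ground for stopping, while 60 of 120 patients are allocated to daily full occlusion of both proximal thighs. It is a cheap patient-safety improvement of minor weight. No sample size, estimate or test is affected.

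The conclusion assumes that the numbered list is the complete set of exclusions, as it is presented, and that criterion 5 reflects an intention to keep compromised thigh vessels away from the cuff. A standard operating procedure that is not shown could already contain such a rule. If so, the change would only bring the published criteria into line with it.

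**What to change.** Extend criterion 5 in Eligibility criteria {10} with the clause: *or current known or suspected thrombosis of a thigh vessel*. The existing drop-out ground then covers later onset without further wording.

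In {11b} and its repeat under {16a}, add: *Patients in whom this arises during the 7 days stop the cuff sessions but stay in follow-up and in the intention-to-treat analysis.* This sentence is not evidence for the point. It only prevents the new clause from removing randomised patients from the analysis.

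**Cost.** The change needs an ethics amendment, for which {25} already provides, and the trial status is still given as in preparation. Slightly fewer patients will be eligible. At the 5 to 6 recruits per month in Recruitment {15}, replacing one patient takes 1/6 to 1/5 of a month. The projection there of up to 180 recruits in 36 months leaves 180 − 120 = 60 in reserve. The wording prescribes no new imaging, but staff will have to decide what counts as suspected.
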